## Discussion

This study protocol follows a single-center, randomized, double-blind, placebo-controlled design. Our objective is to investigate the potential of administering dexamethasone during anesthesia induction to improve postoperative delirium in elderly patients undergoing robot-assisted radical prostatectomy (RARP), enhance sleep quality, and ultimately facilitate enhanced recovery after surgery (ERAS).

It has been shown that prostate cancer is a prevalent urinary tract neoplasm among elderly men, and early surgical intervention is the primary treatment modality [17]. In recent years, minimally invasive surgery techniques, such as robotic-assisted radical prostatectomy (RARP) and laparoscopic radical prostatectomy (LRP), have become increasingly popular, replacing traditional open surgery. However, despite its advantages over traditional surgery, RARP has not significantly reduced many of the anesthesia-related complications associated with surgery. Common postoperative problems among elderly patients undergoing RARP include pain, nausea, vomiting, sleep disturbance, and cognitive decline. Of these, sleep disturbance is particularly prevalent among the elderly and has not been effectively addressed to date.

Research has demonstrated that dexamethasone is an artificially synthesized corticosteroid with potent anti-inflammatory effects, that reduces cortisol secretion before stress stimulation via negative feedback inhibition of the hypothalamus–pituitary–adrenal cortex axis. This reduces the negative effects caused by surgical stress to some extent [18]. Other studies have indicated that preoperative administration of dexamethasone may lower the incidence of POD [12]. Additionally, some studies have reported that elevated serum cortisol levels in the early postoperative period are linked to a heightened risk of cognitive impairment [7, 13]. Therefore, the intravenous administration of dexamethasone during anesthesia induction theoretically has the potential to reduce the release of inflammatory mediators, attenuate the inflammatory response, decrease perioperative cortisol secretion, improve patient sleep quality, and reduce the incidence of postoperative delirium (POD).

There are several limitations in our experimental design. Firstly, patients undergoing robot-assisted radical prostatectomy will be recruited from various surgical teams at Changhai Hospital Urology Center. Due to differences in anatomical sites, surgical techniques, and surgical duration, the surgical trauma experienced by patients may vary, and all of these factors could potentially impact postoperative sleep quality. Secondly, whether patients received preoperative chemotherapy or radiation therapy may also be an important factor influencing postoperative sleep quality.

In our previous study on postoperative nausea and vomiting, we observed that the administration of dexamethasone improved the duration and quality of sleep in patients to some extent. Therefore, we established an experimental group for intravenous injection of dexamethasone in this trial to investigate whether the administration of dexamethasone during induction affects postoperative sleep quality and cognitive function. This study can also serve as a reference for improving the anesthesia program for elderly patients and for further research.

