## Methods

### Trial design

This trial is a single-center, randomized, double-blind, and placebo-controlled study. The study is structured as a parallel grouping with an allocation ratio of 1:1, embracing the framework of a superiority trial.

Changhai Hospital, located in Shanghai, China, is a comprehensive medical institution that integrates clinical practice, teaching, and research. Its Urology Department is among the top-ranking centers in China and is equipped with the most state-of-the-art Da Vinci surgical robot worldwide. Each year, a large number of patients flock to the hospital, drawn by its reputation. Patients who meet the specified criteria will be recruited through recruitment advertisements, with the deadline for recruitment projected to be June 31, 2024. Competent anesthesiologists in specialized preoperative evaluation clinics and wards will be responsible for selecting patients scheduled to undergo robot-assisted laparoscopic radical prostatectomy. We anticipate achieving a recruitment rate of 150%, with an estimated enrollment of 20 patients per month. The expected duration for recruitment is one year. The details of the research plan will not be disclosed to any previously involved medical personnel, and the exclusive responsibility for patient recruitment will be entrusted to specialized anesthesiologists. Patients who fail to meet the inclusion criteria will be excluded. Furthermore, patients who enroll in the trial have the right to discontinue participation and withdraw at any time. If a patient chooses to participate in the trial, they must provide a complete medical history and answer the investigator's questions truthfully. The patient's personal data will be safely stored and protected by the investigator. The trial is expected to be completed by December 2024. Patients will receive detailed information about the study's purpose, risks, and benefits prior to surgery, and must provide written informed consent before initiation of the study. The investigators will complete a case report form (CRF) that includes age (in years), height, weight, and the American Society of Anesthesiologists (ASA) classification. This reported protocol was in accordance with the Standard Protocol Items: Recommendations for Intervention Trials (SPIRIT) guidelines [16].

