### Randomization and blinding

In order to mitigate selection bias, randomization and allocation concealment were conducted by a medical statistician prior to the commencement of the trial. The patients were randomly assigned to two groups in a 1:1 ratio using SPSS 26.0: the dexamethasone group (group D) and the control group (group C). Post-randomization information was sealed in 116 brown paper envelopes and stored in sequence in cabinets. On the day of surgery, the envelopes were opened in sequence based on group assignment and read by an anesthesia nurse on the research team. Dexamethasone or saline was prepared based on the randomization. An anesthesiologist who was blinded to the group assignments conducted the trial. A specialized anesthesiologist performed the outcome assessment, while another anesthesiologist carried out the data analysis. Both of them were unaware of the group allocations. Details regarding patient recruitment advertisement can be obtained from the corresponding author. [name], a valued member of the research team, assumes the pivotal role of patient recruitment. [name] diligently arranges a preoperative visit with the patient the day prior to their scheduled surgery. During this essential preoperative encounter, her primary objective is to ensure that the patients possess a thorough understanding of the study and the clinical significance of their participation, while also obtaining their signed informed consent for the trial.

We will request consent for review of participants' medical records, and for the collection of blood samples to assess Hemoglobin, albumin, serum sodium, testosterone, cortisol, IL-6, TNF, NSE, and Sβ-100 were recorded before surgery, 1 day and 2 day after surgery. The patient's blood specimens will be collected by dedicated laboratory personnel. After proper processing, these samples will be stored in an ultra-low temperature freezer at − 80℃ for subsequent molecular biology experiments and surveillance.

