Follow-up visits will be conducted with registrars who were blinded to group assignment and medication. Data entry for nodal time observation indicators will be completed solely based on the CRF form. The patients’ general condition, such as gender, age, BMI, medical history, height, weight, and AIS score on the night before surgery, will be documented. The heart rate and mean arterial pressure will be measured at four time points: after admission to the operating room (*T*_1_), at the start (*T*_3_), and end (*T*_4_) of surgery, and 30 min after awakening (*T*_5_). The following parameters will be recorded: operative time, anesthesia time, intraoperative blood loss, intraoperative fluid volume, intraoperative dosage of sufentanil and remifentanil, type and dosage of intraoperative vasoactive drug, wake time (time from end of surgery to extubation), and VAS score for resting and coughing 30 min after awakening. All patients will be followed up by a designated person within 72 h after operation. Postoperative sleep quality, sleep duration, and continuity were assessed using the AIS scale and visual analog scale (VAS) score, and analgesic drug doses will be recorded at 24, 48, and 72 h after the operation. Cognitive function will be evaluated using the CAM assessment. Hemoglobin, albumin, serum sodium, testosterone, cortisol, IL-6, TNF, NSE, and Sβ-100 will be measured before surgery, and at 1 and 2 days post-operation.

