### Statistical analysis

We analyzed the data in this study using the statistical software SPSS 26.0. We presented statistical descriptions of the measurement data using either $$\overline{\mathrm{x} }$$±s or median and interquartile range. We performed comparisons between groups using either a two-sample t-test or Mann–Whitney *U* test. We statistically described counting data using rate and constituent ratio. We performed comparisons between groups using either the *χ*^2^ test or Fisher’s exact probability method for pairwise comparisons. We performed comparisons of rank data using the Mann–Whitney *U* test. We analyzed factors associated with POD using logistic regression analysis. In logistic regression analysis, we set α Into as 0.05 and α Out as 0.10. For other hypothesis tests, we considered *P* < 0.05 as statistically significant.

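### Surgical team and prior chemotherapy or radiotherapy are named as possible influences on sleep quality, but the stated randomisation and primary comparison use neither; the cost is a small loss of precision

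*Protocol article*

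**What the plan says.** The limitations paragraph of the Discussion states that "patients undergoing robot-assisted radical prostatectomy will be recruited from various surgical teams at Changhai Hospital Urology Center". It links this to differences in anatomical site, technique, duration and trauma, and says that "all of these factors could potentially impact postoperative sleep quality". It adds that "whether patients received preoperative chemotherapy or radiation therapy may also be an important factor influencing postoperative sleep quality". Sleep quality on the AIS at 24 and 48 h is the primary outcome (Primary outcome). The exclusion criteria do not remove patients with prior chemotherapy or radiotherapy.

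On allocation, Randomization and blinding says: "The patients were randomly assigned to two groups in a 1:1 ratio using SPSS 26.0". The assignments went into 116 envelopes, prepared before the trial and opened in sequence. No stratification factor is named.

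On analysis, Statistical analysis says: "We performed comparisons between groups using either a two-sample t-test or Mann–Whitney *U* test". No covariate is named. The only model is for delirium, a secondary outcome: "We analyzed factors associated with POD using logistic regression analysis".

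On data, Experimental process lists general items such as "gender, age, BMI, medical history, height, weight, and AIS score on the night before surgery", followed by operative time, blood loss and drug doses. Trial design says of participants that "they must provide a complete medical history and answer the investigator's questions truthfully". Neither section lists surgical team or lead surgeon, and neither names chemotherapy or radiotherapy.

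**The concern.** The article identifies two possible sources of variation in its own primary outcome and then describes an allocation and a test that use neither. Both can be known before the study drug is given, so both could be used without conditioning on anything that treatment might change. The recorded intraoperative items cannot take their place. Operative time and blood loss arise after dosing at induction and are themselves listed as secondary outcomes.

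Three things are at stake. Any outcome variance explained by these factors stays in the error term. A chance imbalance between arms has no planned adjustment. If team is not recorded, readers cannot see how it was distributed, and the limitation that the authors raise stays open.

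**Working it through.** **1. The plan's own figure.** Inputs from Sample size calculating: means 5.6 and 6.8, so δ = 1.2; SDs 2.0 and 1.6; Z = 1.96 and 1.28. That section does not name the score; it is taken here to be the AIS, and only the absolute difference is used.
- Pooled variance = (2.0² + 1.6²)/2 = 3.28, SD 1.811.
- n = (1.96 + 1.28)² × 2 × 3.28 / 1.2² = 47.8, so 48 per group, as stated.
- 48 × 1.2 = 57.6, rounded up to the stated 58.

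The figure of 48 reproduces and is not in question here.

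**2. Precision gained by adjustment.** The documents give no share of AIS variance for team or prior therapy. Assume R² = 5–10% jointly.
- Equivalent gain in patients = 1/(1 − R²): 1/0.95 = 1.05 and 1/0.90 = 1.11, so 5–11%.
- Adjusted SD = 1.811 × √(1 − R²). The table gives power at 48 per group for δ = 1.2, two-sided α 0.05, if the pilot SD already contains this variation.

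| R² | Normal approximation | t-based |
|---|---|---|
| 0 (unadjusted) | 90.1% | 89.5% |
| 5% | 91.5% | 90.9% |
| 10% | 92.8% | 92.3% |

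- If the pilot SD does not contain this variation, the trial SD is 1.811/√(1 − R²). Unadjusted power by the normal approximation is then 88.6% at R² = 5% and 86.9% at 10%.

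**3. Chance imbalance.** Assume that one factor (say, the largest team) is present in 20%, 30% or 50% of 116 patients, that is, 23, 35 or 58 patients, split 58 v 58 without stratification. Exact hypergeometric probabilities:

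| Share of patients | Arms differ by ≥ 10 points | Arms differ by ≥ 20 points |
|---|---|---|
| 20% | 16% | 0.4% |
| 30% | 22% | 1.5% |
| 50% | 35% | 4.1% |

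**4. What such an imbalance does to the estimate.** A binary factor with share p that explains R² of a variance of 3.28 shifts AIS by √(R² × 3.28 / [p(1 − p)]).
- Smallest case, p = 0.5 and R² = 5%: √(0.164/0.25) = 0.81 points.
- Largest case, p = 0.2 and R² = 10%: √(0.328/0.16) = 1.43 points.
- A 10-point imbalance moves the group difference by 0.10 × 0.81 = 0.08 to 0.10 × 1.43 = 0.14. That is 7–12% of the planned 1.2.
- The standard error at 48 per group is 1.811 × √(2/48) = 0.37, so the move is 0.2 to 0.4 of a standard error.

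**The case against.** Most of the opposing case stands.

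- **A reader might infer that neither factor is recorded.** The text does not support that. Medical history is recorded and required to be complete, and prior chemotherapy or radiotherapy belongs there. The lists are illustrative rather than exhaustive. Consent is sought for review of medical records (Randomization and blinding), which is a route to the surgeon's identity. The article also says that a fuller protocol exists. Only the narrower statement holds: team is not listed, and prior therapy is not listed by name.
- **A reader might infer that operator effects are established.** The Discussion is hedged throughout. It says these factors may or could matter, and gives neither the number of teams nor the size of any effect.
- **A reader might infer that imbalance could bias or cloud the result.** Randomisation prevents systematic bias, and the standard error of the unadjusted test already allows for chance imbalance, so type I error is unaffected. A 10-point imbalance is quite possible but moves the estimate by less than half a standard error under the assumed R².
- **A reader might infer that the sample size is too small.** The pilot came from the same hospital and research team, so its SD may already contain this variation. The article does not say whether the pilot covered the same operation.

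Unstratified randomisation in a single centre is also an acceptable choice, and the authors disclose the limitation themselves. This does not answer the remaining point: the allocation and test that are stated make no use of pre-dose factors that the article itself considers relevant. Covariates may be set out in an analysis plan that is not shown; if so, the sponsor need only confirm it.

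**Conclusion.** The point holds as an optional improvement in efficiency, not as an error. The unadjusted comparison is valid, and 48 per group reproduces. Under an assumed R² of 5–10%, adjustment for team and prior therapy is worth about 5–11% more patients, or roughly 1.5 to 3 percentage points of power at 48 per group. It also gives a prespecified answer if the arms happen to differ. The size rests wholly on the assumed variance share, for which the documents give no figure. Preoperative AIS, which is already recorded, is a natural further covariate, and its contribution is not included in these figures.

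**What to change.** 1. Put two explicit fields on the CRF: surgical team (lead surgeon code) from the operating list, and preoperative chemotherapy or radiotherapy (yes/no) from the medical history. Complete them retrospectively for patients already enrolled.
2. Before unblinding, prespecify a linear model for AIS at 24 and 48 h with treatment, team (low-volume teams merged), prior therapy and preoperative AIS as covariates.
3. Report the distribution of team and prior therapy by arm.
4. Do not adjust for operative time or blood loss, which arise after dosing.
5. Leave the envelope list unchanged. Re-listing during recruitment would alter allocation mid-trial for little gain.

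The cost is two CRF fields and a few degrees of freedom. The latter is negligible with about 96 analysed patients (2 × 48), provided small teams are merged.

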### Trial status

This study employs Protocol Version 2.0. After receiving ethics approval from the RMIT Human Research Ethics Committee (HREC), recruitment advertising for the study began in July 2022. Recruitment for this study is ongoing, and it is expected to conclude by June 2024.

## Data Availability

The datasets analyzed during the current study and statistical code are available from the corresponding author on reasonable request, as is the full protocol.

## Abbreviations

PSD: Perioperative sleep disorders
POD: Postoperative delirium
RARP: Robot-assisted radical prostatectomy
ERAS: Enhanced recovery after surgery
ASA: American Society of Anesthesiologists
CRF: Case report form
PSQI: Pittsburgh Sleep Quality Index
MMSE: Mini-Mental State Examination
ECG: Electrocardiogram
HR: Heart rate
SpO_2_: Pulse oxygen saturation
IBP: Invasive blood pressure
PACU: Post anesthesia awakening recovery unit
PCIA: Patient controlled intravenous analgesia
AIS: Athens Insomnia Scale
CAM: Confusion assessment method
DMC: Data Monitoring Committee
VAS: Visual analog scale
